Assess the effects of MAPS on hypothesized treatment mechanisms (e.g., motivation, agency/self-efficacy, stress/affect) and the role of those mechanisms in mediating the effect of MAPS on outcomes.

To assess MAPS effects on treatment mechanisms, analyses largely analogous to the GLMM and LMM analyses described for Aim 1 will be conducted. Mediation will be indicated if: (a) there is a significant MAPS effect on the mechanism, and (b) the mechanism significantly predicts the outcome when adjusting for treatment. To formally test for the mediation effect, we will follow appropriate methods described by MacKinnon [95]. In particular, we will use a product-of-coefficients approach in which the indirect (mediation) effect is defined as the product of the coefficient of the intervention condition in the regression of the mechanism (*a* path) and the coefficient of the mechanism in the regression of the outcome variable controlling for intervention condition (*b* path), with appropriate coefficient standardization from *b* path, when the outcome is binary [95]. This approach is applicable for both continuous and binary outcomes (e.g., smoking status, servings of fruits and vegetables, and both self-reported and objectively measured physical activity), with and without repeated measurements. We will use a bootstrapping approach to computing confidence intervals of the indirect effects. Multiple mediator models will be fit to assess simultaneous mediation effects by multiple mechanisms. In addition to the tests for indirect effects, we will also calculate proportion mediated effects and standard errors in both the simple and multiple mediator models.

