### Power

All power analyses assume a significance level of 0.05 and a two-sided test and accounts for a potential 20% attrition at all time points (N = 320; 160/group). Three of the outcomes are continuous (servings of fruits and vegetables, METS of physical activity, accelerometer assessed activity). One outcome (smoking status) is dichotomous. Power is expected to be greater for intent-to-treat analyses than the power reported here, which represents completers only analyses. This is because the total number of cases for intent-to-treat analyses will be 400, versus 320 for the completers only analyses. For intent-to-treat analyses, those lost to follow up will be coded as not abstinent.

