#### Continuous outcomes

Because treatment outcomes are measured at 6, 12, and 18 months, treatment effects may not be consistent across time points. In the case of a constant treatment effect across time, the detectable difference depends on the intraclass correlation coefficient (ICC) between measurements taken from a given participant. Since 160 participants per arm are assumed after attrition, and there are 3 measurements per participant, the effective sample size (ESS) per arm is 3*160/VIF, where VIF is the variance inflation factor 1 + (p-1)*ICC. In this formula, p is the average number of observations per participant. Table 1 shows the minimal detectable constant treatment effect under a range of values for the ICC when testing at a power of 80%. The detectable differences are given in terms of the standard deviation of the error term of the model. Thus, if the ICC is 0.3, the current study has 80% power to detect a shift of 0.229 standard deviations between the treatment arms, a small effect size per Cohen [104]. Power calculations displayed in Table 1 assume approximately consistent effects of treatment across measurements. However, correlations between more distal time points are generally lower than more proximal time points. Thus, calculations presented in Table 1 represent a worst-case scenario. We further computed power for detecting an average intervention difference of 0.3 when the effect varies across time points, specifically, with a shift of 0.1 at 6 months, 0.3 at 12 months, and 0.5 at 18 months. A Geisser-Greenhouse Corrected F Test was used for testing the intervention effect. The estimated power for detecting the treatment effect was 99%, 96%, and 91% for ICC values of 0.1, 0.3, and 0.5, respectively. It is important to note that the presented case of a 0.1, 0.3, and 0.5 increasing difference across time points produces exactly the same power as that of a 0.5, 0.3, and 0.1 decreasing difference across those time points.

**Table 1 T1:** Minimal detectable difference with constant effect

**ICC**	**VIF**	**ESS**	**Detectable difference**
0.0	1.0	480	0.181
0.1	1.2	400	0.198
0.3	1.6	300	0.229
0.5	2.0	240	0.256
1.0	3.0	160	0.314

Note: ICC = intraclass correlation coefficient; VIF = Variance Inflation Factor; ESS = Estimated Sample Size.

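### The proportion mediated (Aim 2, supplementary) is to be reported with standard errors, which describe this ratio poorly when the total MAPS effect is near the 80%-power minimum or smaller

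*Protocol article*

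**What the plan says.** Under Data analysis, Aim 2, the protocol article bases mediation on the indirect effect: "we will use a product-of-coefficients approach in which the indirect (mediation) effect is defined as the product of the coefficient" of the treatment-to-mechanism path and that of the mechanism-to-outcome path. For its uncertainty the article states: "We will use a bootstrapping approach to computing confidence intervals of the indirect effects". The proportion mediated comes at the end of the section, as an addition to those tests: "we will also calculate proportion mediated effects and standard errors in both the simple and multiple mediator models".

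The article does not say whether this standard error comes from the delta method or the bootstrap. Its two conditions for mediation are a MAPS effect on the mechanism and a mechanism that predicts the outcome given treatment. Neither concerns the size of the total MAPS effect, which is the denominator of the proportion.

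**The concern.** The section gives the better-behaved quantity, a product, an interval method that allows for asymmetry. It gives the worse-behaved one, a ratio, a single standard error. A ratio is well summarised by a standard error only if its denominator is many standard errors from zero. The trial is sized so that a detectable total effect may be fewer than three standard errors from zero, and nothing in the text limits the ratio to outcomes with a clear total effect. There are four primary outcomes, so one or more weak total effects is a realistic prospect.

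At stake is how far a reader can trust the stated precision of the share of the MAPS effect credited to motivation, agency or affect.

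**Working it through.** **1. Distance of the denominator from zero.** The inputs are in the Power section. On error rate and attrition: "All power analyses assume a significance level of 0.05 and a two-sided test and accounts for a potential 20% attrition at all time points", leaving 160 per group. On information: "the effective sample size (ESS) per arm is 3*160/VIF, where VIF is the variance inflation factor 1 + (p-1)*ICC", with p = 3. Table 1 gives the "minimal detectable constant treatment effect under a range of values for the ICC when testing at a power of 80"%.

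The detectable difference is (1.960 + 0.842) × √(2/ESS), with ESS = 480/(1 + 2 × ICC).

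| ICC | ESS | Computed | Table 1 |
|---|---|---|---|
| 0.0 | 480 | 0.181 | 0.181 |
| 0.1 | 400 | 0.198 | 0.198 |
| 0.3 | 300 | 0.229 | 0.229 |
| 0.5 | 240 | 0.256 | 0.256 |
| 1.0 | 160 | 0.313 | 0.314 |

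Table 1 is reproduced. The text says the same of ICC 0.3: "if the ICC is 0.3, the current study has 80% power to detect a shift of 0.229 standard deviations between the treatment arms". There the standard error of the total effect is √(2/300) = 0.0816, so z = 0.229/0.0816 = 2.8. Every row has z of about 2.8, because 1.960 + 0.842 = 2.80.

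The article also has a more favourable case: "We further computed power for detecting an average intervention difference of 0.3 when the effect varies across time points". Dividing 0.3 by √(2/ESS) gives z = 4.2, 3.7 and 3.3 for ICC 0.1, 0.3 and 0.5. The implied power is 98.9%, 95.7% and 90.8%, against a stated 99%, 96% and 91%.

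**2. The ratio.** PM = ab/c, where c is the total effect. To first order, SE(PM) ≈ |PM| × √[ var(ab)/(ab)² + var(c)/c² − 2 cov(ab, c)/(ab × c) ]. This SE moves with the estimate. If c is overestimated, PM and its SE are both too small and the interval can lie wholly below the true share. If c is close to zero, PM and its SE are both very large and the interval still covers. Misses therefore fall on one side.

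**3. Simulation, one summary outcome per participant.** Assumptions, none of them in the article: n = 320, one mediator, linear model, b = 0.3 SD, true share 0.3 or 0.5.

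| | z = 2.8 | z about 3.7 (0.3 SD, ICC 0.3) |
|---|---|---|
| Delta-method 95% coverage | about 92-94% | about 93-95% |
| Side of the misses | all below the true share | essentially all below |
| Bootstrap SE above 1.0 | about 42-54% of trials | about 15-25% of trials |

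At z = 2.8 the estimate falls outside 0-1 in 2-8% of trials, and percentile bootstrap intervals cover 97-98%. At z = 2 the estimate falls outside 0-1 in 10-16% of trials, and at z = 1 in 31-33%. With about 600 trials per cell, a percentage near 50 has a simulation error of √(0.25/600), about 2 points.

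**4. Second set-up, using the article's effective sample size.** Assumptions: a path 0.3 or 0.5 SD, true share 0.2, 0.3 or 0.5.

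- *0.229 SD, ICC 0.3, true share 0.3, a = 0.3:* estimates range from about 0.11 to 0.93 (central 95%). The delta-method SE has a median of 0.13 and runs from 0.06 to 1.1 between trials (central 95%). The bootstrap SE runs from 0.09 to 17 (10th to 90th percentile).
- *80%-power effects (ICC 0.3 and 0.5), all shares:* delta-method intervals cover 92-95.5%. Percentile intervals for the proportion cover 96-98%, with median widths of about 0.6 to 1.35.
- *Estimate ± 1.96 bootstrap SE, same effects:* coverage is about 95-97%, reached only because the SE is so often inflated.
- *0.3 SD, ICC 0.3:* the median delta-method SE (0.08-0.15) is close to the true spread (0.085-0.156), with coverage of 94-95%.
- *0.1 SD, ICC 0.3 (z = 0.1/0.0816 = 1.2):* delta-method coverage is 86-90%, and 20-25% of estimates fall outside 0-1.
- *Indirect effect, percentile bootstrap as planned:* coverage is 94-96% at both the 80%-power and the 0.3 SD effects.

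**The case against.** The strongest objection is that this is a small matter about a side statistic. Much of that stands.

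- **Aim 2 inference is untouched.** A reader might infer that the Aim 2 error bars in general, or the mediation conclusions, would be wrong. The documents do not support that. The test is the indirect effect with bootstrap intervals, which perform nominally. No decision rests on the proportion, and the article does not present it as a headline result.
- **z = 2.8 is the minimum, not the whole plan.** Table 1 gives smallest detectable effects. In the 0.3 SD scenario with ICC 0.3 the delta-method SE is close to adequate. To say that the ratio has no stable standard error at the planned effect size would be too broad.
- **The article condenses a fuller plan.** How the SE is computed, and when the ratio is shown, may be settled there. That answers a complaint about missing detail. It does not answer the stated choice of a standard error, which is unsatisfactory under either usual calculation: the delta method misses on one side and the bootstrap SE is unstable.
- **The coverage shortfall is modest.** About 92-94% against 95% is not dramatic, and percentile intervals overshoot to about 97%. The case rests more on the one-sided misses and on an SE that can vary more than tenfold between trials of the same design.
- **Showing the ratio only when the total effect is significant has its own bias.** It selects overestimated denominators. At z = 2.8 the median estimated share fell from 0.51 to 0.465 (true 0.5) and from 0.31 to 0.28 (true 0.3). Suppressing the ratio by a significance rule is therefore not recommended.

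**Conclusion.** The point holds for the proportion mediated alone. Its standard error is a poor measure of uncertainty when the total effect is near the Table 1 minimum, worse for smaller effects, and a milder problem in the 0.3 SD scenario. Nothing in the article keeps the ratio away from outcomes with a weak total effect.

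The exact figures depend on path sizes and true shares that the article does not give, and on a linear single-mediator model. The binary smoking outcome, multiple mediators and explicit repeated measures were not simulated. The direction does not depend on these choices, because it follows from dividing by an imprecise total effect. The consequence is limited to how a supplementary quantity is reported; Aim 1 and the sample size are likewise unaffected.

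**What to change.** In the last sentence of Aim 2, replace the standard errors with percentile bootstrap confidence intervals for the proportion mediated, in both the simple and the multiple mediator models. Take them from the same participant-level resamples as the indirect effect. Always show the indirect and total effects, each with its interval, beside the proportion. Add that the proportion is descriptive and is not interpreted where the interval for the total effect includes zero.

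The cost is one sentence of analysis wording and no new computation of substance, since the bootstrap is already planned. The intervals will look wide, often spanning much of the 0-1 scale, and are slightly conservative at about 97% coverage. That width fairly reflects how little the trial can say about the share when the total effect is small.

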##### Missing data and drop-outs

Some individuals will fail to complete all assessments. GLMM is designed to handle missing data and will give valid inferences for effects provided that the probability of missing data depends only on the observed outcome and/or covariates in the model (or data are missing at random or missing completely at random). We will conduct analyses to examine whether participants who drop out of the study differ from those who do not, and control for those characteristics that are unbalanced between dropouts and completers and believed to be associated with the outcomes. In case where non-ignorable dropout [96] is suspected, our primary analysis approach will use a conservative one of coding the missing outcome as a failure. For example, a missing smoking outcome could be coded as smoking. In addition, we will conduct sensitivity analysis using selection models to account for non-ignorable dropouts. Specifically, we will follow the approach of Diggle and Kenward [97] to model the dropout as a function of both the currently unobserved and previously observed values of the outcome variables (e.g., when dropout is due to lack of improvement in the outcome). Alternatively, we can consider a slope-dependent dropout mechanism [98,99] to account for non-ignorable missingness. In this model, participants are believed to drop out with a high probability if the underlying (unobserved) rate of their change of outcome (e.g., physical activity level) over time is low. In spite of the availability of these potentially useful missing-data handling techniques, we do not expect they will lead to remarkably different results or conclusions given our consistently high follow-up rates [30,100-103].

### Power

All power analyses assume a significance level of 0.05 and a two-sided test and accounts for a potential 20% attrition at all time points (N = 320; 160/group). Three of the outcomes are continuous (servings of fruits and vegetables, METS of physical activity, accelerometer assessed activity). One outcome (smoking status) is dichotomous. Power is expected to be greater for intent-to-treat analyses than the power reported here, which represents completers only analyses. This is because the total number of cases for intent-to-treat analyses will be 400, versus 320 for the completers only analyses. For intent-to-treat analyses, those lost to follow up will be coded as not abstinent.

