### Data analysis

Primary outcomes used to evaluate the efficacy of the MAPS intervention (Aim 1) are smoking status, servings of fruits and vegetables, and both self-reported and objectively measured physical activity assessed at the 6, 12, and 18 months. Because the primary outcomes and mechanisms include repeated measurements that are correlated within subjects, the data analytic approach utilizes generalized linear mixed model regression GLMM; [92,93]. Model diagnostics will be used to determine and address the form of the covariances, transformations, collinearity, and influential observations. GLMM parameter tests will be conducted using Wald statistics, and will be adjusted for multiple comparisons where appropriate. Adjustments for multiple comparisons will be made according to the method of Westfall and Young [94]. In this approach, the correlations among the dependent variables are used to adjust the critical values of the individual tests to ensure that the probability of a Type I error across a set of tests does not exceed the chosen alpha level. This approach has the advantage of maintaining the chosen Type I error rates while at the same time providing a less conservative adjustment than Bonferonni-type procedures.

#### Aim 1

Evaluate the efficacy of a MAPS approach to promoting and facilitating reduction of behavioral risk factors for cancer among high-risk Mexican-origin individuals (overweight/obese smokers). Relative to HE, MAPS is hypothesized to result in positive changes in each of the primary smoking, diet, and physical activity outcomes.

GLMM will be utilized in analyzing the effects of MAPS on the primary outcomes across the 6, 12, and 18-month time points. For the dichotomous outcome, we will assume a logit link and binomial variance function for the GLMM, and parameterize them with blocking on individual nested within treatment condition. Treatment and time will be included, as well as their interaction, with adjustment for relevant covariates as necessary. Time will be treated as a categorical variable. These models test for the main effects of treatment and time, and whether the treatment effect varies over time. For the continuous outcomes, the GLMM analysis will be replaced by linear mixed model (LMM) analysis (i.e., a special case of GLMM in which each outcome variable is continuous).

#### Aim 2

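### All stated power is for an unadjusted two-sided 0.05 test per outcome, although the analysis section announces Westfall-Young adjustment across outcomes

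*Protocol article*

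**What the plan says.** The Power section opens with "All power analyses assume a significance level of 0.05 and a two-sided test". It counts four outcomes: "Three of the outcomes are continuous (servings of fruits and vegetables, METS of physical activity, accelerometer assessed activity"), and then "One outcome (smoking status) is dichotomous". The Continuous outcomes subsection derives Table 1 at 80% power; its worked example, at an ICC of 0.3, is that "the current study has 80% power to detect a shift of 0.229 standard deviations between the treatment arms". It also gives power of 99%, 96% and 91% for an average shift of 0.3. The Binary outcomes subsection gives simulated power for smoking in Table 2. Neither subsection mentions multiplicity.

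The Data analysis section introduces the primary outcomes and then says that the Wald tests will be adjusted for multiple comparisons where appropriate: "Adjustments for multiple comparisons will be made according to the method of Westfall and Young". It explains that the correlations among the dependent variables set the critical values, so that the type I error over a set of tests stays within the chosen alpha. It does not say which tests form the set, or whether the procedure is single-step or step-down. Aim 1 hypothesises a benefit on each primary outcome.

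**The concern.** An adjustment that holds the error rate across several outcomes raises the critical value of at least some of the individual tests. Power computed at 1.96 is then the power of an easier test than the one announced. Because Aim 1 is about each outcome, power per outcome is what a reader will take from the tables.

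At stake is whether the differences that the article calls detectable, and its statement that power for smoking is very good, still hold under its own error control. The other way to reconcile the sections is to leave the primary outcomes unadjusted. The power figures would then stand, but four independent tests at 0.05 carry a familywise error of 1 - 0.95^4 = 18.5%, and the announced protection would not cover the main hypotheses. The two sections need reconciling on either reading.

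**Working it through.** **Inputs from the article.** Two-sided alpha 0.05; 160 completers per arm with three measurements each; "the effective sample size (ESS) per arm is 3*160/VIF, where VIF is the variance inflation factor 1 + (p-1)*ICC"; 80% power for Table 1; four outcomes.

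**Not in the article, so assumed.** Correlation between the test statistics of different outcomes (0 to 0.7, taken as equal for all pairs); single-step or step-down testing (both shown); number of outcomes that respond (one or all four shown).

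**Step 1: reproduce Table 1.** With ESS = 480/(1 + 2 x ICC) per arm and SD = 1, the detectable difference is d = (1.960 + 0.842) x sqrt(2/ESS). For ICC 0.3 this is 2.802 x sqrt(2/300) = 0.229. The table also shows the same differences at alpha 0.05/4 = 0.0125, where z = 2.498.

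| ICC | ESS | Stated d | d at 0.05 | Power of stated d at 0.0125 | d for 80% at 0.0125 |
|---|---|---|---|---|---|
| 0.0 | 480 | 0.181 | 0.181 | 62% | 0.216 |
| 0.1 | 400 | 0.198 | 0.198 | 62% | 0.236 |
| 0.3 | 300 | 0.229 | 0.229 | 62% | 0.273 |
| 0.5 | 240 | 0.256 | 0.256 | 62% | 0.305 |
| 1.0 | 160 | 0.314 | 0.313 | 62% | 0.373 |

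The last row matches at 0.314 when the t distribution replaces the normal. Table 1 is therefore an unadjusted 0.05 calculation. At 0.0125 the power is Phi(2.802 - 2.498) = Phi(0.304) = 0.62, and every detectable difference grows by the factor (2.498 + 0.842)/2.802 = 1.19.

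**Step 2: Westfall-Young over four outcomes.** This was approximated by the maximum of four equicorrelated absolute normal statistics (1,000,000 draws), giving each responding outcome a noncentrality of 2.80, which is 80% power at 0.05.

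| Correlation | Critical value | Single-step | Step-down, one responds | Step-down, all four respond |
|---|---|---|---|---|
| 0 | 2.49 | 62% | 62% | 73% |
| 0.3 | 2.48 | 63% | 63% | 72% |
| 0.5 | 2.44 | 64% | 64% | 72% |
| 0.7 | 2.38 | 66% | 67% | 73% |

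The range is 62-73%. At a correlation of 0.95 with all four responding it reaches 76%.

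**Step 3: average shift of 0.3.** The noncentrality 0.3 x sqrt(ESS/2) is 4.243, 3.674 and 3.286 for ICC 0.1, 0.3 and 0.5. Subtracting 1.960 gives power of 98.9%, 95.7% and 90.8%, which matches the stated 99/96/91%. Subtracting 2.498 gives 96.0%, 88.0% and 78.5%. The last becomes 78.9% at a critical value of 2.483 (correlation 0.2), hence about 96/88/79%.

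**Step 4: Table 2.** Each stated power was shifted by Phi(z_power + 1.960 - 2.498). This gives 0.79 to 0.61, 0.84 to 0.68, 0.94 to 0.85, 0.95 to 0.87, 0.98 to 0.94 and 0.99 to 0.96. It is only an approximation: the article does not name the test behind its simulation, and an attempt to reproduce the table matched only some cells.

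**The case against.** The strongest reply is that the adjustment applies only where appropriate, that no family is named, and that an exact family is commonly left to the analysis plan, which is not shown. On that view nothing is contradicted, and Table 1 is correct at its declared alpha. Part of this stands. Table 1 contains no arithmetic error, and the four-outcome family is an inference. It remains the natural reading: the paragraph starts from the primary outcomes, describes the method as working across dependent variables, and serves an aim stated for each outcome. Nor is this a detail left to the analysis plan, because the article itself states both the adjustment and the power.

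Three stronger readings are tempting and are not supported.

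- **That the trial's true power is 62-73%.** The figure depends on an undefined family, an unstated correlation, the form of the procedure and the number of responding outcomes. Two of the four outcomes measure physical activity, so some correlations may be high.
- **That the adjustment makes success on all four outcomes unlikely.** The article does not make joint success a criterion, and if it did, no adjustment would be needed. With 80% unadjusted power per outcome and zero correlation, the chance of all four is 41% unadjusted and 38% under step-down. The low figure comes almost entirely from requiring four successes.
- **That the family is five, because two fruit and vegetable instruments are listed.** The Power section counts fruit and vegetable servings as one outcome.

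**Conclusion.** The point holds as a mismatch between sections: the power printed is not that of the tests announced. Its size is conditional on the four primary outcomes forming the family. The loss is material for the Table 1 differences and for the ICC 0.5 smoking cells with constant or increasing differences; the article calls increasing differences the most likely pattern. It is modest elsewhere. The average-shift scenario keeps about 79% or more, and the ICC 0.3 detectable difference stays below 0.3 SD. The results for the continuous outcomes rest on calculations that reproduce the article's own figures. Those for smoking are indicative only. Nothing here shows that the sample size is untenable.

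**What to change.** State in the Data analysis section that the four primary outcomes form the Westfall-Young family. Recompute Table 1, the 99/96/91% figures and Table 2 at the adjusted level, and report the results as the trial's power. Alpha 0.0125 is a safe bound that needs no assumption about correlation or about single-step versus step-down testing. Table 2 should be re-simulated with the intended test, not shifted by the approximation used here. Keep N = 400. The cost is a revision of text and tables plus one rerun of the simulation; the downside is that the stated power becomes less favourable.

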#### Binary outcomes

National data suggest that approximately 5% of the general population of smokers quit each year [105]. However, smokers in HE receive a brief treatment based on national recommendations [22]. Therefore, we estimate that the abstinence rate for HE will be approximately 5%, 10%, and 15% across the three follow-ups (i.e., 10% quit rate per year). Power calculations for correlated binary outcomes are more complex than continuous outcomes, which require simulations. For example, it is not possible to have the same ICC between all pairwise observations. Therefore, the mean of all pairwise ICC values was used as the overall ICC and looked at three potential scenarios based on the simulation of 1000 trials. Using the estimated quit rate for HE of 5%, 10%, and 15% across the three follow-ups, Table 2 shows simulation results for constant, increasing, and decreasing differences between arms for each time point at ICC values of 0.1, 0.3, and 0.5. For cessation induction trials such as this one, the most likely scenario would be increasing differences over time given that 80-90% of smokers will not be motivated to quit at Baseline. Regardless, power is very good for detecting reasonable and meaningful differences between groups under realistic scenarios.

**Table 2 T2:** Simulation results

	**Constant differences**				**Increasing differences**				**Decreasing differences**		
	**6 months**	**12 months**	**18 months**		**6 months**	**12 months**	**18 months**		**6 months**	**12 months**	**18 months**
**HE**	0.05	0.10	0.15	**HE**	0.05	0.10	0.15	**HE**	0.05	0.10	0.15
**MAPS**	0.15	0.20	0.25	**MAPS**	0.10	0.20	0.30	**MAPS**	0.20	0.20	0.20
**difference**	0.10	0.10	0.10	**difference**	0.05	0.10	0.15	**difference**	0.15	0.10	0.05
**ICC**	**power**	**95% CI**		**ICC**	**power**	**95% CI**		**ICC**	**power**	**95% CI**	
**0.10**	0.99	0.98**-**1.00		**0.10**	0.99	0.98	1.00	**0.10**	0.99	0.98**-**1.00	
**0.30**	0.94	0.93**-**0.95		**0.30**	0.95	0.94	0.96	**0.30**	0.98	0.97**-**0.99	
**0.50**	0.79	0.76**-**0.82		**0.50**	0.84	0.82	0.86	**0.50**	0.98	0.97**-**0.99	

Note: HE = Health Education; MAPS = Motivation And Problem Solving; ICC = intraclass correlation coefficient; CI = confidence interval.

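### The reason given for expecting higher intent-to-treat power fails for smoking abstinence: the 80 added cases are all coded as failures, so under equal 20% whole-participant loss power is slightly lower, not higher.

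*Protocol article*

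**What the plan says.** The Power section sets the frame: "All power analyses assume a significance level of 0.05 and a two-sided test", and the calculation "accounts for a potential 20% attrition at all time points (N = 320; 160/group". It lists four outcomes, one dichotomous (smoking status) and three continuous: "Three of the outcomes are continuous (servings of fruits and vegetables, METS of physical activity, accelerometer assessed activity". It then compares two analysis sets without limiting the comparison to any one outcome: "Power is expected to be greater for intent-to-treat analyses than the power reported here, which represents completers only analyses". The reason follows at once: "This is because the total number of cases for intent-to-treat analyses will be 400, versus 320 for the completers only analyses". The next sentence fixes the coding: "For intent-to-treat analyses, those lost to follow up will be coded as not abstinent".

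Under Binary outcomes, the control-arm assumption is "we estimate that the abstinence rate for HE will be approximately 5%, 10%, and 15% across the three follow-ups". Table 2 pairs these rates with three sets of MAPS rates: "Table 2 shows simulation results for constant, increasing, and decreasing differences between arms for each time point at ICC values of 0.1, 0.3, and 0.5". No size is given for the expected intent-to-treat gain, and no attrition by arm.

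**The concern.** The argument treats 400 cases as if each carried the same information as the 320 completers. Under the stated coding, none of the 80 extra cases can be a success. They raise the denominator and lower both abstinence rates, so the treatment difference shrinks as the sample grows. The net effect on power has to be worked out and cannot be read off the case count.

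At stake is how a reader takes Table 2. The sentence presents the table as conservative, with the intent-to-treat analysis expected to do better. One cell (constant difference, ICC 0.5) is already at 0.79, and a reader would expect intent-to-treat to lift it. The coding may also govern the main result: the section on missing data and drop-outs makes failure coding the primary approach when non-ignorable dropout is suspected.

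**Working it through.** **Inputs.** Two-sided alpha 0.05, 20% attrition, 160 completers per group and 400 randomised (Power section); abstinence rates from Table 2. Assumptions: 1:1 allocation (200 per arm), equal loss in both arms (implied by 160 per group), and lost participants missing all three visits. The last two are relaxed under the objection.

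**Reproducing the plan's figure.** Take the arm difference in abstinence averaged over the three visits. Per arm, the variance is (1/9) × [Σ p_j(1−p_j) + 2·ICC·Σ_{j<k} s_j s_k] / n, with s_j = √(p_j(1−p_j)). For the constant scenario at ICC 0.3, the bracket divided by 9 is 0.04613 (HE) and 0.08415 (MAPS). So SE = √(0.13029/160) = 0.02854, z = 0.10/0.02854 = 3.504, and power = Φ(3.504 − 1.960) = 0.939. Table 2 states 0.94.

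**One visit, algebra.** Completers have rate p and variance p(1−p)/160. Under failure coding the rate is 0.8p and the variance 0.8p(1−0.8p)/200. The variance ratio is 0.64(1−0.8p)/(1−p), which exceeds 0.64 for any p > 0. The squared difference is multiplied by exactly 0.64, so the test statistic falls. With a common p, the ratio of z values is √[(1−p)/(1−0.8p)], below 1.

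**One visit, numbers** (unpooled normal approximation):

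| HE vs MAPS | 160 completers | 200, lost = not abstinent | 200 at undiluted rates |
|---|---|---|---|
| 10% vs 20% | z 2.53, 71.6% | z 2.48, 69.9% | z 2.83, 80.7% |
| 15% vs 25% | z 2.25, 61.6% | z 2.20, 59.3% | z 2.52, 71.2% |
| 15% vs 30% | z 3.27, 90.4% | z 3.16, 88.5% | z 3.65, 95.5% |

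All seven distinct visit-level comparisons in Table 2 fall under this coding.

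**Averaged over visits.** When a lost participant is zero at every visit, each between-visit covariance becomes 0.8·cov + 0.16·p_j p_k. For the constant scenario at ICC 0.3, the per-arm terms are 0.03851 and 0.07372. So SE = √(0.11223/200) = 0.02369, z = 0.08/0.02369 = 3.377, and power = 0.922. Other cells:

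| Scenario | ICC | Completers | Lost = not abstinent |
|---|---|---|---|
| Constant | 0.3 | 0.939 | 0.922 |
| Increasing | 0.3 | 0.945 | 0.928 |
| Decreasing | 0.3 | 0.937 | 0.920 |
| Constant | 0.5 | 0.881 | 0.861 |
| Increasing | 0.5 | 0.890 | 0.871 |
| Decreasing | 0.5 | 0.878 | 0.858 |

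The ICC 0.1 cells fall too (constant: 0.981 to 0.970). A 1,000-trial GEE simulation gives the same sign in all nine cells (constant, ICC 0.3: 0.930 to 0.916).

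**Where the expected gain comes from.** Counting 200 per arm at the undiluted rates gives 80.7% for 10% versus 20%, and 0.975 for constant, ICC 0.3. That calculation contradicts the coding rule stated in the same paragraph.

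**Limit of the reproduction.** Table 2 does not fully specify its test. The approximation gives 0.881 where the table states 0.79 (constant, ICC 0.5) and 0.878 where it states 0.98 (decreasing, ICC 0.5). The completer-to-ITT differences are therefore guides to direction and rough size, not replacements for Table 2 entries.

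**The case against.** A reader might infer that failure coding always lowers power, so that Table 2 is a ceiling. The documents do not support that, for three reasons.

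- **Pattern of missingness.** The protocol says only 20% at all time points and does not say that the same people miss every visit. If 20% are missing independently at each visit, the between-visit covariance becomes 0.64·cov, and the scattered zeros weaken the within-person correlation. Averaged power then rises above that of 160 full completers: constant, ICC 0.5, 0.881 to 0.904; ICC 0.3, 0.939 to 0.948. At ICC 0.1 it is flat.
- **Unequal loss.** No arm-specific loss is given. For constant, ICC 0.3, a loss of 22% in HE and 18% in MAPS gives 0.952, while 15% in HE and 25% in MAPS gives 0.788, against 0.939 for completers. A rise from greater HE loss is bias created by the coding, not information.
- **Continuous outcomes.** A reader might also infer that these gain nothing. That is essentially true only of participants with no follow-up at all. The plan's own effective-sample-size formula uses the average number of observations per participant. With 200 per arm averaging 2.4 visits it gives 480/(1 + 1.4·ICC). At ICC 0.3 that is 338 against 300, and the detectable difference improves from 0.229 to 0.215. Four hundred full cases would give 600/1.6 = 375 and 0.205, so the gain is real but partial.

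It is also fair to say that no numeric margin is claimed, that Tables 1 and 2 already use 160 per group, and that Table 2's interval for its weakest cell is 0.76 to 0.82, wider than the effect at issue.

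What stands is that the stated reason, 400 cases against 320, is invalid for abstinence under the stated coding, and that under the equal split implied by the plan, with whole-participant loss, the stated direction is wrong.

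**Conclusion.** The point holds in a limited form. For smoking abstinence, with equal 20% loss, lost participants missing all follow-ups and coded as not abstinent, intent-to-treat power is about 1 to 2 points below completer power. The protocol says it will be above. Against what a simple count of 400 would suggest, the shortfall is larger: 80.7 − 69.9 = 10.8 points at the 10% versus 20% visit, and 0.975 − 0.922 = 0.053 averaged over visits (constant, ICC 0.3).

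The sign is not fixed once loss is unequal or missed visits are scattered. It would also go too far to say by how much the 0.79 cell drops, because the approximation does not reproduce that cell. For the continuous outcomes, the case count alone does not justify the claim, though some gain from partial follow-up is possible.

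Severity is minor. The sample size does not rest on the expected gain, and neither the design nor the analysis changes.

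**What to change.** 1. Delete the sentence expecting greater intent-to-treat power, together with its case-count reason.
2. State instead that, with equal 20% whole-participant loss and missing coded as not abstinent, intent-to-treat power for abstinence is slightly lower than in Table 2, and that other dropout patterns can move it either way.
3. Rerun the Table 2 simulation with 200 per arm under that coding, name the assumed dropout pattern, and report the result as an added row.
4. State that power for the three continuous outcomes rests on participants with follow-up data.

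The cost is a few sentences, one rerun of an existing simulation, and slightly less favourable stated power for abstinence.
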